### Secondary Outcome

The results of the cost-benefit analysis can be considered a secondary outcome. Conducting a cost-effectiveness analysis allows for the assessment of the economic implications and potential cost savings associated with deferring postoperative follow-up visits. This outcome provides insights into the financial feasibility and efficiency of implementing the deferred follow-up strategy.

We will perform a cost-benefit analysis to compare the economic status of the intervention group and active control group. For this we have to collect financial data on direct and indirect costs. Data on direct costs will be retrieved from the hospital record system, because this is the money paid directly by patients for their treatment after the surgery is recorded, including payments for consultation, medicine, and investigation (if required) at each follow-up visit.

Data on indirect costs, that is, costs incurred to the patient in the process of coming to the follow-up visit, include the following: (1) lost productivity costs (how much money the patient could have earned if the patient hadn’t come to the hospital follow-up visit), (2) transportation costs (the cost incurred while travelling), and (3) companion costs (patients will definitely have a companion, for whom we also have to calculate both costs above (lost productivity and transportation). Data on indirect costs will be obtained from interviews with the patients. We will calculate the average cost per visit, which will ultimately reveal the costs and benefits of the new approach, because the suggested new regimen will eliminate one follow-up visit.

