## Results

More than 526 participants will be enrolled in the study, with a minimum of 263 assigned to the intervention group (deferred follow-up visits) and a minimum of 263 to the comparison group (standard practice of early postoperative follow-up visits). The sample will have diverse demographics, ensuring a representative population.

Visual acuity measurements will be obtained for both groups during the follow-up period. We will be able to statistically compute whether the deferred follow-up visit group demonstrates comparable visual acuity outcomes to the comparison group. This will be inferred if there are no statistically significant differences between the two groups in terms of visual acuity outcomes (*P*>.05).

Among the participants in the deferred follow-up visit group, the number of patients who experience postoperative complications during the 4-week follow-up period will be compared with the group with the 1-week follow up visit.

We will also determine if participants in the deferred follow-up visit group report high levels of satisfaction with the extended recovery period and reduced travel burden. The number of participants who express that deferring follow-up visits provided them with convenience and comfort during the recovery phase will be mentioned.

We will determine if reduction in early postoperative visits allows health care providers to allocate their time and expertise more efficiently, focusing on patients with immediate needs or complex postoperative care requirements.

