## Discussion

### Expected Findings

The proposed study will investigate the feasibility and potential benefits of deferring postoperative follow-up visits up to 4 weeks after uneventful cataract surgery in a tertiary level eye hospital in Kavrepalanchok.

Deferring postoperative follow-up visits will allow patients to recover in the familiar environment of their homes, reducing the need for immediate travel and associated costs. This can have a positive impact on patient satisfaction and comfort during the recovery period. By avoiding unnecessary trips to the hospital, patients may experience reduced anxiety and stress, leading to an improved overall experience.

By spacing out follow-up visits, health care providers can optimize resource allocation within the tertiary level eye hospital. This approach will allow health care personnel to allocate their time and expertise more efficiently, focusing on patients who require immediate attention or complex postoperative care. Moreover, it can potentially reduce the burden on health care facilities, as fewer appointments are scheduled during the early postoperative period.

Deferring follow-up visits may also improve access to care, particularly for patients residing in remote areas. Traveling to health care facilities shortly after surgery can be challenging, especially for individuals with limited mobility or limited access to transportation. By extending the follow-up period, patients from distant locations can receive necessary care without the immediate need for travel, increasing the likelihood of their adherence to follow-up appointments.

One major concern related to deferring follow-up visits is the potential delay in detecting postoperative complications. Early postoperative visits allow health care providers to closely monitor patients for any signs of infection, inflammation, or other adverse events. When extending the follow-up period, it is crucial to educate patients regarding the signs and symptoms of postoperative complications so that they can visit the hospital, if required, on time. Patients should receive comprehensive information about self-care, potential warning signs, and instructions on when to seek medical attention. This will empower patients to actively participate in their own recovery and promote a sense of responsibility for their eye health.

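### The only cost calculation the plan fixes takes the saving from the visit schedule, so extra unscheduled visits or complication treatment in the deferred group cannot reduce it

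*Protocol article*

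**What the plan says.** The Secondary Outcome section of the protocol article opens its cost plan with a between-group aim: "We will perform a cost-benefit analysis to compare the economic status of the intervention group and active control group". Direct costs come from the hospital record system, "including payments for consultation, medicine, and investigation (if required) at each follow-up visit". Indirect costs come from patient interviews and are defined as "costs incurred to the patient in the process of coming to the follow-up visit": earnings forgone, travel, and the same two items for the accompanying person.

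The section ends with the calculation: "We will calculate the average cost per visit, which will ultimately reveal the costs and benefits of the new approach", and the reason it is thought sufficient is "because the suggested new regimen will eliminate one follow-up visit".

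Two other places bear on this. Results plans a comparison of complications by group, as counts of patients: "the number of patients who experience postoperative complications during the 4-week follow-up period will be compared with the group with the 1-week follow up visit". Expected Findings, under Discussion, wants staff to "educate patients regarding the signs and symptoms of postoperative complications so that they can visit the hospital, if required, on time". Neither is carried into the cost calculation.

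**The concern.** A mean cost per visit says nothing about how many visits each group makes. To turn it into a saving, one needs the difference in visits per patient, and the section supplies that number from the schedule: one. The estimate is therefore positive by construction. It cannot come out as no saving or as a loss, and it does not use the comparison that randomisation provides.

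Specific objective 3 is a cost-benefit analysis of the intervention, and the Abstract's Conclusions already looks forward to reporting lower expenses for patients. The method as fixed cannot test that expectation. The events that could erode the saving are ones the article itself foresees: patients returning on their own initiative, and complications found late because the early visit was dropped.

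**Working it through.** **Inputs.** From Study Design, Setting, and Participants: after randomisation group 1 has two scheduled visits (1 week and 1 month) and group 2 has one (1 month). The article states no visit cost, no unscheduled-visit rate and no complication cost, so there is no figure of the plan's own to reproduce. All rates and relative costs below are assumptions.

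**Notation.** c is the cost of a routine visit, u1 and u2 are unscheduled visits per patient in groups 1 and 2, and m is the cost of an unscheduled visit, with any treatment it brings, in units of c. All scheduled visits are taken as attended and equally costly.

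**Saving as the plan derives it.** c × 1 = c, for any u1, u2 and m.

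**Saving per patient.**
- Group 1: 2c + m·u1·c
- Group 2: c + m·u2·c
- Difference: c[1 - m(u2 - u1)]

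The plan overstates the saving by m(u2 - u1) visit costs when group 2 has the higher unscheduled rate. It is unbiased when the rates are equal, and understates the saving when group 1 has the higher rate.

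**Results with c = 1, against the plan's 1.00.**

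| u2 - u1 | m = 1 | m = 2 | m = 5 |
|---|---|---|---|
| 0.05 | 0.95 | 0.90 | 0.75 |
| 0.10 | 0.90 | 0.80 | 0.50 |
| 0.20 | 0.80 | 0.60 | 0.00 |

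For example, m = 2 and u2 - u1 = 0.20 gives 1 - 2 × 0.20 = 0.60. The saving vanishes when m(u2 - u1) = 1.

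**If unscheduled visits enter the average.** The article does not say which visits are averaged. Suppose all are pooled, with u1 = 0, u2 = 0.10 and m = 5. Total cost is 2 for group 1 and 1 + 0.5 = 1.5 for group 2, over 2 + 1.1 = 3.1 visits. The mean is 3.5/3.1 = 1.13, which would be read as the saving, while the per-patient difference is 2 - 1.5 = 0.50. On that reading, costly events in the deferred group raise its apparent benefit.

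**The case against.** The strongest reply is that the section does promise to compare the groups, and that an article may leave the estimator of a secondary economic outcome to a fuller document. The first half is true, so it would be wrong to say the plan contains no between-group cost comparison. The fault is that the calculation it then names does not deliver one. The second half does not dispose of the point, because the article commits to a method and gives a reason for it. How the confidence interval is computed can fairly be left elsewhere.

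Several stronger readings are tempting but are not supported:

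- *Unscheduled visits and complication treatment are excluded from the data.* Nothing excludes them. The hospital's record of payments after surgery may hold them, and the list of direct costs is introduced as inclusive. They fail to count because of the summary measure. The indirect items, however, are tied to coming for the follow-up visit.
- *The plan writes the saving as mean visit cost times one.* No such formula appears. It is inferred from the stated reason, which has no other natural reading.
- *The average mixes day 7 and day 30 visits.* The text does not say so, and a separate day 7 mean would fit it.
- *Group 1 patients who skip day 7 shrink the saving further.* Exclusion criterion 5 removes patients who miss follow-up visits, so that loss would not appear in the analysed set. Whether that exclusion is sound is a separate question.
- *All unscheduled visits in group 2 count against deferral.* The guidance on warning signs is not limited to group 2, so group 1 patients may also return. Only the excess u2 - u1 matters.
- *Deferral probably costs more.* At m of 1 to 2 and an excess of up to 0.20 the saving stays positive. In the table it reaches zero only at m = 5 with an excess of 0.20, and eligibility is restricted to uncomplicated surgery without relevant eye disease.

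**Conclusion.** The point holds in this form: the section announces a comparison of the groups but fixes a calculation that infers the benefit from the schedule. The outcome is a saving of about one average visit cost, insensitive to any difference between the groups in unscheduled visits or complication treatment.

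Under assumed values of 0.05 to 0.20 excess unscheduled visits per deferred patient, each costing one to two routine visits, the actual saving is 0.95 to 0.60 of a visit, an overstatement of 0.05 to 0.40. The size, and even the direction, of the bias depends on quantities that the document does not give. What does not depend on them is that the planned calculation cannot show a null or adverse cost result. This concerns a secondary outcome and should be corrected. It does not touch the visual acuity comparison.

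**What to change.** Replace the closing sentence of the Secondary Outcome section with a comparison, between the randomised groups, of mean total direct plus indirect cost per patient from day 1 through the final visit. Count every scheduled and unscheduled visit and all treatment, and give a 95% confidence interval for the difference. Record the same cost items at unscheduled visits as at scheduled ones, using the existing hospital records and interview questions.

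The cost is slightly more recording. Indirect costs come from interviews, so they will be incomplete for patients who do not return, and the report should state how many are affected in each group. The reported saving may be smaller than one visit's cost, but it would be an observed result of the trial.

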### Plan for Use of Research Findings

Research findings will be disseminated through the Reiyukai Eiko Masunaga Eye Hospital newsletter. Donors will be also informed. Results will be published in high-impact journals for better coverage.

### Ethical Considerations

#### Ethical Approval

The Declaration of Helsinki will be adequately addressed. Ethical approval for this study has been obtained from the ethical review board of the Nepal Health Research Council (428/2022 P).

#### Consent

Participants will be provided with detailed information about the study, including the deferral of postoperative visits, as well as potential risks, benefits, and alternatives. A written informed consent form will be provided to all participants.

#### Privacy and Confidentiality

Study data will be collected and stored in a manner that ensures the anonymity or deidentification of participants. Personally identifiable information such as names, addresses, and social security numbers will be removed from the data set. Each participant will be assigned a unique identifier that is used instead of their personal information.

## Results

More than 526 participants will be enrolled in the study, with a minimum of 263 assigned to the intervention group (deferred follow-up visits) and a minimum of 263 to the comparison group (standard practice of early postoperative follow-up visits). The sample will have diverse demographics, ensuring a representative population.

Visual acuity measurements will be obtained for both groups during the follow-up period. We will be able to statistically compute whether the deferred follow-up visit group demonstrates comparable visual acuity outcomes to the comparison group. This will be inferred if there are no statistically significant differences between the two groups in terms of visual acuity outcomes (*P*>.05).

Among the participants in the deferred follow-up visit group, the number of patients who experience postoperative complications during the 4-week follow-up period will be compared with the group with the 1-week follow up visit.

We will also determine if participants in the deferred follow-up visit group report high levels of satisfaction with the extended recovery period and reduced travel burden. The number of participants who express that deferring follow-up visits provided them with convenience and comfort during the recovery phase will be mentioned.

We will determine if reduction in early postoperative visits allows health care providers to allocate their time and expertise more efficiently, focusing on patients with immediate needs or complex postoperative care requirements.

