## Methods

### Study Design, Setting, and Participants

This will be a prospective, quantitative, experimental, noninferiority control study of health services use. Selected patients undergoing cataract surgery at Reiyukai Eiko Masunaga Eye Hospital irrespective of the type of surgery (SICS or phacoemulsification) will be included in the study.

All enrolled patients will undergo an examination on the first postoperative day conducted by an ophthalmologist who is unaware of the patient’s group assignment. Subsequently, the patient will proceed to the counselor’s office, where a unique identification number will be generated and the patient will be randomized into either group 1 or group 2.

In group 1, patients will be instructed to attend follow-up visits at 1 week and 1 month postoperatively. In group 2, patients will be instructed to attend a follow-up visit at 1 month postoperatively only. During the visit, the patients will receive detailed guidance on the appropriate use of medications and be educated about the signs and symptoms they should be vigilant for. The specific date of the postoperative visit will also be communicated.

At each follow-up visit, the patient will directly visit the counselor’s office. Upon arrival, they will be provided with a blank sheet of paper containing the unique identification number assigned to them on the first postoperative day. Visual acuity testing will be conducted by a blinded optometrist, while slit lamp biomicroscopy will be performed by a blinded ophthalmologist. Before leaving the hospital, the patient will return the paper to the counselor, who will then enter the necessary information into the patient’s file. 

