### Exclusion Criteria

Patients will be excluded if (1) there are complications during the surgery that warrant more frequent follow-up visits (eg, premature entry, posterior capsular rupture, zonular dialysis, postoperative hyphema, toxic anterior segment syndrome, or postoperative fibrin in the anterior chamber); (2) the surgery is for complicated cataract, traumatic cataract, ocular hypertension, or if the patient has drug allergies; (3) the patients has a history of diseases that might affect postoperative visual outcomes, such as uveitis, glaucoma, viral keratitis, corneal scarring, hypertensive retinopathy, diabetic retinopathy, central retinal vein occlusion, branched retinal vein occlusion, or age-related macular degeneration; (4) the patient is unwilling to participate or does not provide written consent; and (5) the patient misses the follow-up visits.

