### Sample Size and Sampling Technique

Sample size is calculated as follows: 2[Zα + Z1 – β] 2 × (sd2/d2) = 2 [1.96 + 1.645 ] 2 × [(0.1125)2/(0.025)2] = 263 for one group, where reference mean values for postoperative visual outcomes are taken from the study conducted by Deshpande et al [25]. The number of participants in intervention group will be 263 and the number of participants in the control (reference) group will be 263. We will use a random sampling technique and computer-generated random numbers to assign patients to the intervention or control group. We generated randomized numbers with a commonly used method [26]. The assignment will be done by the counsellor on the first postoperative day. The researchers will be masked as to randomization at all postoperative visits.

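### At the stated minimum of 263 assigned per group the implied 95% power is not delivered: mainly because the printed formula gives 526 per group, and further because patients who miss visits are dropped with no stated allowance

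*Protocol article*

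**What the plan says.** The section Sample Size and Sampling Technique prints the calculation as "2 [1.96 + 1.645 ] 2 × [(0.1125)2/(0.025)2] = 263 for one group" and turns the result directly into the trial's size: "The number of participants in intervention group will be 263 and the number of participants in the control (reference) group will be 263". The Results section repeats the figure as a floor at randomisation, "with a minimum of 263 assigned to the intervention group (deferred follow-up visits) and a minimum of 263 to the comparison group", within a total given only as more than 526.

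The fifth item under Exclusion Criteria excludes a patient if "the patient misses the follow-up visits". Study Design, Setting, and Participants and the sample-size section both place randomisation on the first postoperative day, before any later visit can be missed. The article gives no expected attendance, no inflation for loss and no replacement rule. Power is not stated in words; it is implied by the multiplier 1.645.

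**The concern.** A formula of this kind returns the number of patients per group who must contribute an outcome. Here the same number is counted at assignment, and a separate rule then removes assigned patients. At the stated minimum, one missed visit in a group takes the number analysed below 263.

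The power implied by the calculation would then not be the power of the analysis. This matters because the design is described as a "prospective, quantitative, experimental, noninferiority control study of health services use", while comparability is to be inferred from "no statistically significant differences between the two groups in terms of visual acuity outcomes (*P*>.05". If a real difference exists, a smaller analysed group makes that result more likely, so an overstated power lends the conclusion more weight than it has earned.

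**Working it through.** **Inputs.** From the sample-size section: Zα = 1.96 (two-sided 5%, or one-sided 2.5%), Z for power = 1.645 (95%), SD = 0.1125, d = 0.025. From Results: at least 263 assigned per group. Assumed, because the article gives no figure: 10% and 20% loss.

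**1. The plan's own figure.** n per group = 2 × (1.96 + 1.645)² × (0.1125 / 0.025)² = 2 × 12.996 × 20.25 = 526.3.

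The printed 263 is not reproduced. It appears if the leading 2 is left out (12.996 × 20.25 = 263.2), or if 526 is taken as the total and halved. Lower power does not explain it: 90% power needs 426 per group and 80% needs 318. Reading d as a noninferiority margin, with a true difference of zero and one-sided 2.5%, gives the same size as the two-sided test (527 after rounding up).

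**2. Power at the number analysed.** Power = Φ( d / (SD × √(2/n)) − 1.96 ), where n is the number analysed per group. For n = 263: SD × √(2/263) = 0.00981; 0.025 / 0.00981 = 2.548; 2.548 − 1.96 = 0.588; Φ(0.588) = 0.722. The 95% interval half-width is 1.96 × 0.00981 = 0.0192.

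| Assigned per group | Assumed loss | Analysed per group | Power | 95% CI half-width |
|---|---|---|---|---|
| 263 | 0% | 263 | 72% | 0.0192 |
| 263 | 10% | 237 | 68% | 0.0203 |
| 263 | 20% | 210 | 62% | 0.0215 |
| 526 | 0% | 526 | 95% | 0.0136 |
| 526 | 10% | 473 | 93% | 0.0143 |
| 526 | 20% | 421 | 90% | 0.0152 |

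**3. Separating the two causes.** With no loss, using 263 in place of 526 costs 95 − 72 = 23 percentage points. Starting from 526, loss alone costs about 2 points at 10% and 5 points at 20%. Starting from 263, it costs a further 4 and 10 points (72 to 68, and 72 to 62).

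**4. If the calculated number is to be analysed, how many must be assigned.** Number assigned = n / (1 − loss), rounded up. For 263: 263 / 0.9 gives 293 and 263 / 0.8 gives 329. For 527, which is 526.3 rounded up: 586 and 659.

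**The case against.** The strongest reply is that attrition is the smaller part of this. The fall from 95% to 72% happens with every patient analysed, and it comes from the sample-size arithmetic. Taken alone, 10% to 20% loss from a correctly sized trial leaves power at about 90% or more. That stands, and the two causes have to be reported apart.

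Second, a reader might infer that the analysed groups will certainly fall below the required number. The article does not support that. Both enrolment figures are floors, so over-enrolment could make up for missed visits. Because missing visits is listed as an exclusion, the 263 participants in the sample-size section could also be read as patients who remain eligible. The word assigned in the Results section tells against that reading, and the possible excess is not quantified, but a shortfall is a possibility and not a demonstrated fact.

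Third, a reader might infer that every lost patient makes a finding of comparability easier. That holds only if there is a true difference. With none, P>.05 occurs about 95% of the time at any sample size. The weakness of that decision rule is a separate matter.

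Fourth, the article's Discussion presents travel soon after surgery as difficult and suggests that deferral may improve adherence. It is no evidence of poor one-month attendance. Expected attendance or an enrolment margin may also be given in the full protocol, which is not shown. That limits what can be said about the likely loss. It does not reconcile the three things the article does fix: the number, the point at which it is counted, and the rule that removes patients afterwards.

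**Conclusion.** The point holds in a limited form. At the stated minimum of 263 assigned per group, the implied 95% power is not delivered. The ceiling is 72% with complete attendance, because the printed formula gives 526 per group. Dropping patients who miss visits lowers it further, to about 68% at 10% loss and 62% at 20%. Correcting 263 to 526 without addressing loss would still leave about 93% or 90%.

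These figures rest on the plan's own d, SD and 5% level, on equal loss in both groups, and on loss rates that are assumptions. Enrolment above the floors would soften or remove the part due to loss. With 263 assigned, attributing the whole gap from 95% to attrition would overstate attrition's role.

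**What to change.** In Sample Size and Sampling Technique and in Results, state that 263 per group is the number assigned. Replace the implied 95% with the power at the number expected to be analysed: at most 72%, and about 68% and 62% at 90% and 80% attendance. In the report, give the numbers analysed in each group and the width of the confidence interval achieved.

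This changes wording only. Its cost is a less favourable stated power, and it does not restore 95%. If the calculated number is instead defined as patients analysed, the plan must say that more have to be assigned, on the scale shown in step 4 of the working. That option is not free of extra patients.

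The fifth exclusion criterion may also remove patients unequally, since group 1 has two scheduled follow-up visits to miss and group 2 has one. That is a possible bias, which neither the rewording nor a larger sample would cure, and it needs its own resolution.

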**Methods:**

A prospective, quantitative, experimental control study will be carried out in Reiyukai Eiko Masunaga Eye Hospital, located in Banepa, Kavrepalanchok, Nepal. All patients undergoing cataract surgery meeting the inclusion and exclusion criteria irrespective of the type of surgery (small-incision cataract surgery or phacoemulsification) will be included in the study. The patients will be randomly assigned to 1 of 2 groups. Patients in group 1 will be examined on day 1, day 7, and day 30, whereas patients in group 2 will be examined on day 1 and once between days 25 to 30. The minimum clinically important difference (MCID) in our study will be set according to the improvement in the Snellen visual acuity chart.

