**Results:**

The study is expected to be completed within 6 to 8 months from the start of the project. Data analysis and report writing will be carried out in a 2-month period. Best-corrected visual acuity will be compared between the 2 groups to determine if the MCID is achieved. The cost-effectiveness of the new approach will also be analyzed.

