**Conclusions:**

We aim to conclude that we can safely defer the 1-week postoperative follow-up visit in patients undergoing uncomplicated cataract surgery and that, moreover, we can reduce the patient load at the hospital and decrease patient expenses by decreasing the frequency of hospital visits.

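### A study labelled noninferiority will infer comparable acuity from P>.05, a rule that cannot show noninferiority; how much this matters depends on a margin that the article does not give

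*Protocol article*

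**What the plan says.** Under Study Design, Setting, and Participants the protocol article fixes the framework: "This will be a prospective, quantitative, experimental, noninferiority control study of health services use". The Results section then states how comparable acuity in the deferred group will be decided: "This will be inferred if there are no statistically significant differences between the two groups in terms of visual acuity outcomes", with P>.05 given as the criterion.

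The abstract carries a second criterion. Its Methods paragraph says "The minimum clinically important difference (MCID) in our study will be set according to the improvement in the Snellen visual acuity chart", and its Results paragraph says "Best-corrected visual acuity will be compared between the 2 groups to determine if the MCID is achieved". No value is given, and neither sentence is linked to the P>.05 rule.

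The sample-size section prints "2 [1.96 + 1.645 ] 2 × [(0.1125)2/(0.025)2] = 263 for one group". The 0.025 has no unit and is not called a margin. The Results section repeats the size: "More than 526 participants will be enrolled in the study, with a minimum of 263 assigned to the intervention group". The conclusion aimed for in the abstract is "We aim to conclude that we can safely defer the 1-week postoperative follow-up visit in patients undergoing uncomplicated cataract surgery".

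**The concern.** Noninferiority is a claim that the new schedule is not worse by more than a stated amount. It is shown when the confidence limit for the difference excludes that amount. P>.05 in a difference test says only that the data are compatible with no difference; they may equally be compatible with a relevant loss. Under such a rule, lower precision makes the favourable conclusion easier to reach.

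Visual acuity is named as the most important primary outcome, and the Introduction presents the study as a safety evaluation of changing standard follow-up. A practice-changing conclusion would therefore rest on a rule whose error rate depends on the SD and on how many patients are analysed. The Exclusion Criteria remove patients who miss follow-up visits, so the number analysed may fall below the number assigned.

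This is not detail left to an unseen analysis plan. The article states the rule outright, and the rule conflicts with the design label.

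**Working it through.** **Inputs.** SD = 0.1125, d = 0.025, z = 1.96 and z = 1.645 (Sample Size and Sampling Technique); 263 per group (same section and Results); P>.05 as the rule (Results). Assumptions made here: d = 0.025 serves as the margin, a positive difference means the deferred group is worse, and the normal approximation holds.

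**1. The plan's own figure.**
- (1.96 + 1.645)² = 12.996 and (0.1125/0.025)² = 20.25.
- 2 × 12.996 × 20.25 = 526.3 per group. The printed 263 appears only without the leading 2: 12.996 × 20.25 = 263.2.
- So 263 per group is about half of what the formula gives. This is a separate error, but it affects the figures below.

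**2. Chance that P>.05 accepts a true deficit of 0.025.** With SE = SD × √(2/n), the chance is Φ(1.96 − 0.025/SE) − Φ(−1.96 − 0.025/SE). The second term is negligible.

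| n per group | SD | SE | 0.025/SE | P>.05 rule accepts |
|---|---|---|---|---|
| 526 (formula) | 0.1125 | 0.00694 | 3.60 | 5.0% |
| 263 (stated) | 0.1125 | 0.00981 | 2.55 | 27.8% |
| 210 (assumed, about 20% not analysed) | 0.1125 | 0.01098 | 2.28 | 37.6% |
| 263 | 0.20 (assumed) | 0.01744 | 1.43 | 70.0% |

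**3. Confidence-limit rule at the same margin.** It accepts when the observed difference + 1.96 SE is below 0.025. If the true difference is 0.025, the chance is Φ(−1.96) = 2.5% in every row.

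**4. One result at 263 per group.** The half-width is 1.96 × 0.00981 = 0.0192. An observed deficit of 0.015 gives z = 1.53 and P = .13, which counts as comparable. Its 95% CI is −0.004 to 0.034, which does not exclude 0.025. The largest deficit that passes, 0.0192, has an upper limit of 0.0385.

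**5. Dependence on the margin.** The same formula with a larger true deficit gives:
- deficit 0.05, SD 0.1125, 263 per group: 0.05/0.00981 = 5.10, accepted in 0.09%;
- deficit 0.1, SD 0.1125, 263 per group: z = 10.2, accepted in essentially 0%;
- deficit 0.1, SD 0.20, 263 per group: z = 5.73, accepted in 0.008%.

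**6. Power of the confidence-limit rule if the true difference is 0 and the margin is 0.025.** At 263 per group: Φ(0.025/0.00981 − 1.96) = Φ(0.588) = 72%. The 95% implied by z = 1.645 needs 527 per group.

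**The case against.** Four points can fairly be made for the plan.

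- **The MCID text.** The abstract intends a comparison against an MCID, so the authors do have a relevant difference in mind. That is true, but without a value or a confidence-limit test it does not replace the P>.05 rule. It leaves two unreconciled criteria.
- **The 27.8% is not the rule's doing alone.** A reader might infer that the rule has no control at all over false acceptance. The documents do not support that. The formula uses z = 1.645, that is, 95% power at d = 0.025; with the 526 per group it yields, the rule would accept a true 0.025 deficit in 5.0% of trials. Most of the excess comes from the halved sample size. What stands is narrower: this control holds only if the planned SD and sample size are achieved, whereas a confidence-limit rule does not need them.
- **The harm may be small.** A reader might infer that a small or noisy trial would often pass a schedule that costs a full line of vision. At a margin of 0.1 the false-acceptance risk is near zero, even with SD 0.20. The large percentages hold only for a margin near 0.025, and the article names no margin.
- **The stress cases are not in the plan.** Neither an SD of 0.20 nor 210 per group appears in it, and the article promises a minimum of 263 assigned per group. Both are assumptions. Some loss is plausible because patients who miss visits are excluded, but its amount is not given.

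The rule can also err the other way, but only under a wider margin. At 263 per group an observed deficit of 0.03 gives z = 3.06, P = .002 and an upper limit of 0.049. This fails P>.05 although it would satisfy any margin above 0.049. It cannot be combined with the 0.025 illustration, because each assumes a different margin.

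**Conclusion.** The point holds. The stated rule contradicts the stated design, and P>.05 is not evidence of noninferiority at any margin. The unquantified MCID does not repair this.

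The size is conditional. If 0.025 is the margin and the SD is 0.1125, the rule accepts a deficit equal to the margin in 27.8% of trials at the stated 263 per group, against 2.5% for a confidence-limit rule. At the 526 per group from the printed formula it would be 5.0%. It rises to 38% at an assumed 210 per group and to 70% at an assumed SD of 0.20. At a margin of 0.1 it is close to zero. The documents therefore support calling the rule invalid for its purpose; they do not support 28% as the trial's actual error rate.

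**What to change.** Replace the P>.05 sentence in the Results section with wording such as:

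> Noninferiority is concluded if the upper limit of the two-sided 95% CI for the mean difference in final-visit best-corrected visual acuity (group 2 minus group 1, on the named acuity scale, higher = worse) lies below a numeric margin fixed before unblinding and derived from the stated MCID. P>.05 is not evidence of comparability.

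Three items must accompany it, since the sentence cannot be applied without them:
- a justified numeric value for the MCID and for the margin derived from it;
- the acuity scale, because the abstract names only the Snellen chart and the sample-size inputs have no unit;
- the power for that margin at the planned n, for example 72% at 263 per group if the margin is 0.025 and the true difference is 0.

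**Cost.** The rule change itself needs no extra data. It is more than a one-sentence edit, because the margin and scale must be justified and the stated power may become less favourable. If the margin were 0.025 and 95% power were to be kept, the size would be 527 per group, about double the current plan.
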